#### Exclusion criteria

Patients with sensory and/or coagulation disorders, a history of spinal surgery, heart complications, concurrent severe central or peripheral nervous system disease, epilepsy, needle phobia, serious pathologies that can be the main cause of chronic low back pain (for example, presence of lumbar stenosis, spondylolisthesis, tumours, etc.), or patients contraindicated for transcutaneous electrical stimulation (TENS) will be excluded.

### Randomization and blinding

Participants will be randomized to two groups using a computer-generated (Epidat 4.2) table of random numbers generated. After randomization, participants will be assigned to either the experimental electrical dry needling group or the conventional physiotherapy control group in a ratio of 1:1. Randomization will be performed by the principal investigator.

There will be 46 participants in each group. The randomly generated group allocations will be placed in sealed opaque envelopes before being delivered to the participants and stored in locked cabinets.

The outcome assessor and study statistician will be blinded to the entire process. The outcome assessor will make no attempt to guess the participant’s treatment group. The computer-generated outcome measures transmitted to the statistician will not contain any information that identifies the patient’s group.

### Interventions

After the initial evaluation, 92 patients with CLBP will be randomly assigned to one of the two groups and will receive electrical dry needling (experimental group) or conventional physiotherapy (control group). All participants will receive 1 session per week for 6 weeks, until they have received a total of 6 sessions. Patients must complete 100% of their scheduled face-to-face treatment sessions, and those in the control group must also complete 80% of the home exercise sessions in order to remain in the intention-to-treat analysis.

During the study, participants can only receive their assigned treatment; they cannot combine the study treatment with medications or any other treatment. Any interference in the treatment will be grounds for exclusion. Patients may abandon the study at any time, and the assigned interventions may be suspended or modified in a particular trial patient in response to improvement or deterioration (adverse effects) of low back pain. Adverse events will be reported to the principal investigator, who will monitor the affected patients and the possible causes of these events.

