#### Inclusion criteria

Both male and female patients aged between 30 and 65 years with chronic low back pain lasting 3 months or more, with a low back pain disability score ≥ 4 on the Roland-Morris Disability Questionnaire (RMQ) and not receiving any other physiotherapy treatment are eligible for inclusion.

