### Conventional physiotherapy group

Patients assigned to the conventional physiotherapy group (*n* = 46) will receive ischaemic compression and analytical stretching of the quadratus lumborum, multifidus and iliocostal muscles once a week for a total of 6 weeks.

Ischaemic compression will consist of constant pressure stimulation with the thumb on each MTrP for between 30 s and 2 min. This compression sequence will be repeated several times. The intensity of the pressure will be adjusted to a level at which each subject reports “comfortable pain”, in order words, between the pain threshold and the maximum tolerable pain [36, 45] (see Additional file 1 for the analytical stretching procedure).

These patients will also be given a dossier of home lumbar spine exercises to be performed 5 days a week for a total of 6 weeks (Additional file 2: dossier of home exercises). To monitor compliance, patients will be instructed to note down in a booklet the dates on which they complete the exercises in the dossier.

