### Data analysis

Statistical analysis will be performed using SPSS© version 21.0 and STATA 14 using the principles of intention to treat. Comparisons will be made between the two study arms. We will calculate the difference between the groups after the final treatment session and at 2 months post-intervention (short-term results).

The efficacy variable for this clinical trial is the difference between continuous variables (i.e., RMDQ, ODI, VAS, TSK, SF-36, PSQI, HADS, pressure algometry, McQuade test and trunk range of movement) at baseline and at predetermined time points (electric dry needling treatment vs conventional physiotherapy):

The Kolmogorov-Smirnov test will be used to assess the normality of continuous variables.

The equality of means of the intragroup hypotheses will be analysed using Student’s *t* test for paired clinical variables in the case of parametric distributions and the Kruskal-Wallis *H* test in the case of nonparametric distributions.

One-way analysis of variance (ANOVA) will be used to test the intragroup hypothesis in the case of parametric distributions, and the Kruskal-Wallis *H* test will be used in nonparametric distributions.

Post hoc analysis will be obtained for parametric distributions and Mann-Whitney *U* for nonparametric distributions.

The confidence interval will be set at 95% and the level of significance at 0.05.

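### The set labelled intention to treat is limited to patients who complete treatment, with an extra home-exercise condition in the control arm only

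*Protocol article*

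**What the plan says.** Protocol article, Data analysis: the analysis will be done "using the principles of intention to treat". That section does not define the analysis set further.

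Protocol article, Interventions, supplies the membership rule. For both arms: "Patients must complete 100% of their scheduled face-to-face treatment sessions". For controls, in addition: "those in the control group must also complete 80% of the home exercise sessions in order to remain in the intention-to-treat analysis".

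Protocol article, Conventional physiotherapy group: controls receive a "dossier of home lumbar spine exercises to be performed 5 days a week for a total of 6 weeks". Compliance is self-recorded: "patients will be instructed to note down in a booklet the dates on which they complete the exercises". The section on the electrical dry needling group describes no home exercise.

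Two further statements in Interventions bear on who might leave. Combining the study treatment with medication or any other treatment is not allowed, and "Any interference in the treatment will be grounds for exclusion". The assigned intervention may also be "suspended or modified in a particular trial patient in response to improvement or deterioration" of the low back pain.

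**The concern.** Intention to treat means that everyone randomised is analysed in the arm to which they were allocated. A set that patients stay in only by adhering is a per-protocol set, whatever it is called. Adherence is observed after randomisation and may be related to prognosis, motivation and early response, so conditioning on it gives up the protection of randomisation.

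The one-arm condition makes this worse. If both arms were filtered by the same rule with the same effect, the selection could largely cancel. Here a control who keeps all clinic visits but skips home exercise is removed, while a comparable patient in the needling arm stays. The primary comparison would then be between differently selected subgroups, and readers would be told that it was an intention-to-treat result.

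**Working it through.** **1. The passages side by side.** Data analysis names intention to treat. Interventions sets adherence conditions for staying in the analysis of that name. Nothing elsewhere in the article reverses or qualifies those conditions, so following the text as written gives a completers analysis.

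**2. The extra control condition.** 5 days x 6 weeks = 30 home sessions, and 80% of 30 = 24. A control with 23 recorded sessions is out. The needling arm has no equivalent.

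**3. How many controls might be lost to that condition.** The document gives no adherence rate. Assume that each home session is completed independently with probability q. The share retained is P(Bin(30, q) ≥ 24):

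| Assumed q | Share of controls retained |
|---|---|
| 0.90 | 97% |
| 0.85 | 85% |
| 0.80 | 61% |
| 0.75 | 35% |

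The result is very sensitive to q, so one-arm loss could be trivial or large.

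**4. What unequal retention could do.** From the document: 46 randomised per arm, SD 2.5 RMDQ points (Sample size section), two-sided alpha 0.05. Assumed: no true difference; an adherence score correlated r = 0.3 to 0.5 with improvement; in each arm the most adherent share k is kept, with k = 0.85 for needling and 0.70, 0.60 or 0.50 for control.

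The mean shift in a retained arm is SD x r x φ(z_k)/k, where z_k is the normal quantile of k. The values of φ(z_k)/k are 0.2743 (k = 0.85), 0.4967 (0.70), 0.6439 (0.60) and 0.7979 (0.50).

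- Bias = 2.5 x r x [φ(z_C)/k_C − φ(z_E)/k_E].
- SE = 2.5 x √[1/(46 k_E) + 1/(46 k_C)].
- Type I error ≈ 1 − Φ(1.96 − bias/SE) + Φ(−1.96 − bias/SE).

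Example, 85% v 70%, r = 0.3: bias = 2.5 x 0.3 x (0.4967 − 0.2743) = 0.17. SE = 2.5 x √(1/39.1 + 1/32.2) = 0.595. Type I error = 0.059.

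| Retention, needling v control | Bias, r = 0.3 to 0.5 (RMDQ points) | Type I error |
|---|---|---|
| 85% v 85% | 0 | 5% |
| 85% v 70% | 0.17 to 0.28 | 5.9 to 7.5% |
| 85% v 60% | 0.28 to 0.46 | 7.3 to 11.5% |
| 85% v 50% | 0.39 to 0.65 | 9.2 to 16.9% |

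With positive r the bias favours control. Nearly all the excess rejections lie on that side: at 85% v 50% and r = 0.5 they are 16.8% favouring control and 0.2% favouring needling. With negative r (patients who feel better stop exercising) the signs reverse.

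**5. Whether a true intention-to-treat set is affordable.** The plan allows for 15% loss: 46 x 0.85 = 39.1, about 39 per arm. Power for the planned 2.5 points = Φ(2.5/(SD√(2/39)) − 1.96). This is 99% with SD 2.5, and 94% with SD √10 = 3.16, since the Sample size section also states a variance of 10. Either exceeds the 85% target.

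**The case against.** The core is hard to contest, because the article attaches the adherence conditions to the intention-to-treat analysis by name. Several stronger readings are tempting, and the document does not support them.

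- **Every listed exclusion removes the patient from the analysis.** Only the attendance and home-exercise sentence says so. Being grounds for exclusion could mean exclusion from treatment, from the study or from the analysis. A patient whose treatment is suspended or modified may or may not fail a rule about that patient's own scheduled sessions. If such patients are removed, the loss would be related to outcome, but the text leaves this open.
- **One missed visit ends membership.** Interventions says that sessions continue until six have been received, which may allow make-up visits. Multiplying a per-session attendance rate over six visits may therefore overstate the loss, and no such figure is relied on here.
- **The medication ban is stricter than the entry rules.** The Inclusion criteria alone ("not receiving any other physiotherapy treatment are eligible for inclusion") might suggest that only other physiotherapy is barred at entry. The Participants section, however, already limits recruitment to patients under no current treatment of any kind.
- **The inflated error rate favours needling.** If adherent controls improve more, the bias works against the trial's own hypothesis.

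It is also fair to say that the calculation depends on assumed retention and correlation, and that if the two arms retain similar patients the bias is small. All of this limits the supporting claims. None of it removes the contradiction or the one-arm condition.

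**Conclusion.** The concern holds. The Interventions rule contradicts the principle named in Data analysis, and as written the primary comparison is a completers comparison with an additional condition in one arm, under an intention-to-treat label. This conclusion rests on the wording alone.

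The size and direction of the bias cannot be derived from the document. The illustrative range is about 0.17 to 0.65 RMDQ points, against a planned difference of 2.5, with type I error of about 6 to 17%. It depends on the assumed retention (85% against 70% to 50%), the assumed correlation of 0.3 to 0.5 and SD 2.5, and it would be near zero if both arms were selected alike. It should not be read as a prediction, or as evidence that the rule favours either arm.

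**What to change.** 1. In Interventions, delete the closing clause that makes the attendance and home-exercise thresholds a condition for staying in the intention-to-treat analysis.
2. Define the primary analysis set as all randomised patients, analysed in their allocated arm. Collect both scheduled follow-up assessments from everyone, whatever their attendance, home exercise, use of other treatment, or suspension or modification of the intervention.
3. Use the 100% and 80% thresholds and the interference rule only to define a separately named, secondary per-protocol set, and say explicitly that exclusion under the interference rule means exclusion from that set alone.
4. Interventions gives six sessions for all participants, while the section on the electrical dry needling group gives a maximum of three within the same six weeks. These passages must be reconciled so that completing all scheduled sessions has a clear meaning in the per-protocol set.

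Whether an individual patient's treatment stops is a clinical matter and is not affected by this change.

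Cost: protocol wording, reported as an amendment under Ethics and dissemination, and inviting non-adherent patients to visits that are already planned. No extra patients are needed. The downside is that the effect estimate may be somewhat diluted by non-adherence.

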### Participants

A total of 92 patients aged between 30 and 65 years, diagnosed with nonspecific chronic low back pain lasting more than 3 months [40] who are not currently undergoing any type of treatment, will be recruited. Patients will be randomized to two treatment groups (electrical dry needling or conventional physiotherapy). Participants will receive treatment once a week for 6 weeks in the physiotherapy laboratories of the University of Almería, with a follow-up evaluation at 6 weeks and 2 months after the start of treatment. During their first visit, participants will be screened for study eligibility according to the study inclusion and exclusion criteria and will be assessed by a therapist blinded to the interventions. After this face-to-face evaluation, patients will be randomly assigned to one of the two groups and will receive the corresponding treatment for low back pain administered by two researchers trained in the techniques used. All participants will sign the informed consent form, which complies with the Declaration of Helsinki of the World Health Organization (schedule of enrolment, interventions and assessments is shown in Fig. 1).

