**Screening and enrolment**							
Eligibility screen RPTs	✓						
Informed consent	✓						
Eligibility screen face to face to blinded evaluator		✓					
Allocation principal investigator		✓					

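### Excluding patients who take medication or other treatment during the study most plausibly removes randomised patients, against the stated intention-to-treat principle

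*Protocol article*

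**What the plan says.** The Interventions section first describes the random assignment of 92 patients. Its opening paragraph ends with a condition: all scheduled sessions, plus 80% of home exercise in controls, must be completed "in order to remain in the intention-to-treat analysis".

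The next paragraph concerns conduct during the study. Participants may receive only the assigned treatment; "they cannot combine the study treatment with medications or any other treatment". Then comes the rule at issue: "Any interference in the treatment will be grounds for exclusion". The same paragraph goes on to voluntary withdrawal and to suspending or modifying the intervention.

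The Data analysis section says the analysis will be done "using the principles of intention to treat".

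Treatment at entry is described in different terms in different places. The Participants section refers to patients "who are not currently undergoing any type of treatment, will be recruited". The Inclusion criteria are narrower: those "not receiving any other physiotherapy treatment are eligible for inclusion". The Exclusion criteria contain no medication item; their last entry reads "or patients contraindicated for transcutaneous electrical stimulation (TENS) will be excluded". Table 1 lists two eligibility screens, one labelled "Eligibility screen RPTs" and one face to face with the blinded evaluator, without saying which rule is applied at which.

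**The concern.** Intention to treat keeps every randomised patient in the assigned arm, whatever else the patient takes. A rule that removes patients for co-treatment after allocation is incompatible with it.

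Medication use at baseline is balanced between arms by randomisation, in expectation. Use after allocation has no such protection. A patient whose back pain persists has a reason to take an analgesic, so removal can depend on outcome. It can also depend on arm: the Randomization and blinding section names only the outcome assessor and the statistician as blinded, and a patient can tell needles with current from thumb compression, stretching and home exercise. All three primary outcomes (RMDQ, ODI, VAS) are reported by the patient. Wording that calls interference a ground for exclusion, without naming who decides, also leaves room for judgement after allocation.

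Perfect screening would not remove the problem, because a patient untreated at entry can start an analgesic later.

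**Working it through.** **Reading the text**

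1. The rule stands under Interventions, after the random assignment, and covers the period during the study. Eligibility has its own sections. The rule therefore acts on patients already allocated.
2. The text does not say what the patient is excluded from. The preceding paragraph makes adherence a condition of staying in the intention-to-treat analysis, so the authors use that term for a set from which patients can be removed.
3. Nothing in the article says that excluded patients are still followed up or analysed.
4. Removal from the study and the analysis is thus the most plausible reading, and it contradicts the Data analysis section.

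**Supporting point on eligibility.** Staff who apply the Participants sentence would not enrol a medicated patient. Staff who apply only the listed criteria could, and that patient would then meet the exclusion rule after allocation.

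**Size of a possible bias**

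The article has no figure to reproduce here, because it gives no rate of co-treatment. The exclusion shares and outcome gaps below are assumptions.

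Let p be the share excluded in an arm and d the mean RMDQ of excluded patients minus that of retained patients. Then

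retained mean = full-arm mean − p × d.

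For needling (A) minus control (B):

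bias = pB × dB − pA × dA.

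A higher RMDQ score is worse, so a positive bias works against needling.

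Inputs from the article: planned difference 2.5 points; SD 2.5; 46 per arm; 15% loss to follow-up. The Sample size section also mentions a variance of 10, which implies SD √10 = 3.16, so both values are used. Per arm before these exclusions: 46 × 0.85 = 39.1, taken as 39. This assumes that the 15% loss does not already include them.

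| pA, pB | dA, dB | Bias | Share of 2.5 | n after exclusion (A, B) | Type I error, SD 2.5 | Type I error, SD 3.16 |
|---|---|---|---|---|---|---|
| 10%, 10% | 2.5, 2.5 | 0.25 − 0.25 = 0 | 0% | 35.1, 35.1 | 5.0% | 5.0% |
| 5%, 10% | 2.5, 2.5 | 0.25 − 0.125 = 0.125 | 5% | 37.0, 35.1 | 5.5% | 5.3% |
| 5%, 15% | 2.5, 2.5 | 0.375 − 0.125 = 0.25 | 10% | 37.0, 33.1 | 7.0% | 6.2% |
| 10%, 10% | 1.0, 3.5 | 0.35 − 0.10 = 0.25 | 10% | 35.1, 35.1 | 7.0% | 6.2% |

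The type I error is that of a two-sided t test at 0.05 when the true difference is zero and the estimate is shifted by the bias. At SD 2.5 the standard error is 2.5 × √(1/nA + 1/nB): 0.589 in the second row, 0.598 in the third and 0.597 in the fourth.

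The last row shows that equal numbers excluded per arm do not rule out bias. Swapping the arms reverses the sign and leaves the size unchanged. In the rows with bias 0.25, at SD 2.5, the 7.0% consists of 6.1% false results in the favoured direction and 0.9% in the other.

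**Power.** Removing 15% or 30% of the 46 per arm leaves power for 2.5 points at 0.993 or 0.980 with SD 2.5, and at 0.938 or 0.887 with SD 3.16. All are above the 85% target, so within this range the concern is bias more than lost power.

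**The case against.** The strongest reply is that the conflict is inferred. The rule never mentions the analysis. Where the authors mean the analysis set they name it, and they do so in another paragraph about attendance and home exercise. The sentence after the rule deals with withdrawal and with suspending an intervention, so exclusion might mean only that study treatment stops, which intention to treat can accommodate. The article is also a condensed document, and the handling of withdrawn patients is often left to the full protocol or analysis plan. This much stands: the meaning is not certain. But the rule is stated, not missing, and nothing in the article says that these patients stay in follow-up or analysis. Even on the milder reading their outcomes could be lost.

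A second reply is that the attendance and home-exercise condition is the more explicit breach of intention to treat. That is true, and it needs its own correction. The trigger here is different, though, and the co-treatment rule would remain in force once the adherence condition was corrected.

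Third, the entry rules can be read together: the Participants sentence is simply stricter, and a patient can satisfy both. That is fair, and the eligibility wording is only a supporting point.

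Fourth, the magnitudes rest on assumptions, the biased scenarios in the table all work against needling, and patients helped by an analgesic could score lower than those retained, which would reverse the gap. All of this stands. The direction cannot be predicted, and the illustrated sizes are modest.

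**Conclusion.** The concern holds, with medium confidence because the article does not define exclusion. On its most plausible reading, the co-treatment rule removes randomised patients for behaviour that can depend on arm and outcome, against the article's own analysis principle. The actual bias cannot be known from the article. Under the assumed shares and gaps it lies between 0 and 0.25 RMDQ point in either direction, at most 10% of the planned difference, with type I error of at most 7.0% at SD 2.5 or 6.2% at SD 3.16. That is a defect that should be corrected, though on these figures it would not by itself overturn a true 2.5-point effect.

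**What to change.** - **Interventions section:** replace the exclusion rule. Medication or other treatment taken after randomisation should be recorded as a protocol deviation; the patient stays in follow-up and in the intention-to-treat analysis in the assigned arm. Any analysis restricted to patients without co-treatment should be secondary and labelled per protocol.
- **Inclusion criteria:** carry over the no-current-treatment condition from the Participants section, naming medication, so that it is applied before allocation.

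The cost is a change of wording, one screening question and possibly a few more screening failures.

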#### Primary outcome measures

The following are the primary outcome measures:
Roland Morris Disability Questionnaire (RMDQ): This self-reported questionnaire consists of 24 items that rate limitations in different activities of daily life attributed to low back pain, such as walking, bending over, sitting, lying down, dressing, sleeping, personal care and daily activities. Disability is rated from 0 points (best) to 24 points (worst) [46].Oswestry Disability Index (ODI): The Oswestry Disability Index assesses the limitations in activities of daily living in 10 dimensions, each rated on a 6-point scale (0–5 points). The higher the score, the greater the disability. The overall score is expressed as a percentage and is used to classify people as minimally disabled (0–10%), moderately disabled (20–40%), severely disabled (40–60%), crippling back pain (60–80%) or bedridden (80–100%) [47].Visual analogue scale (VAS): Study participants will indicate the intensity of their pain on a 100-mm VAS. They are asked to situate their pain on a 100-mm horizontal line, where 0 mm indicates “no pain”, and 100 mm indicates “the worst pain imaginable” [48].

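### Medication or other treatment after randomisation is a ground for exclusion, but the protocol does not say from what; if from the analysis, the rule conflicts with intention to treat and can bias the comparison

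*Protocol article*

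**What the plan says.** Under Interventions, the protocol article says of participants during the study that "they cannot combine the study treatment with medications or any other treatment". The next sentence reads: "Any interference in the treatment will be grounds for exclusion". Interference is not defined; from its position it most likely means the use of such treatment. The object of the exclusion is not stated.

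Three other statements bear on how to read it:

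- The paragraph before, also under Interventions, requires all face-to-face sessions in both arms, and 80% of home exercise sessions in the control arm, "in order to remain in the intention-to-treat analysis".
- The sentence after the rule says that patients may leave the study and that "the assigned interventions may be suspended or modified in a particular trial patient", in response to improvement or deterioration of low back pain.
- Data analysis says that the analysis will be done "using the principles of intention to treat" and makes no exception for patients who take other treatment.

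Nothing in the article says that a patient excluded under this rule is still assessed or still analysed.

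**The concern.** The rule acts after randomisation, on behaviour that probably depends on how the patient is doing. Someone whose back pain is not improving is more likely to take an analgesic or seek other care. The primary outcomes are pain ("Study participants will indicate the intensity of their pain on a 100-mm VAS") and disability on the RMDQ and ODI. If such patients leave the analysis, those who remain are partly selected on outcome, and the groups compared are no longer the groups that were randomised.

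The trigger is also separate from the attendance and home-exercise rule. A patient who attends all 6 sessions and completes the home exercises could still be excluded for one course of medication, so correcting only the attendance sentence would leave this route open.

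**Working it through.** **1. What the exclusion is from.** Setting the statements side by side:

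- *For exclusion from study and analysis:* the previous paragraph shows that this protocol does remove randomised patients from its analysis for conduct after randomisation, and no statement retains excluded patients.
- *For withdrawal from treatment only:* the rule stands in a paragraph on concomitant care, and the next sentence concerns suspending or modifying the intervention. Data analysis states intention to treat without exception.

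The first reading conflicts with Data analysis; the second does not. The article does not decide between them.

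**2. Size of the bias if patients leave the analysis.** The article gives no rate of such use, so there is no stated figure to reproduce. The following is illustration only.

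Inputs from the article: RMDQ standard deviation (SD) 2.5, or √10 = 3.16 from the variance of 10 (Sample size); 46 per arm (Randomization and blinding).

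Assumptions made here: no true difference; the proportion *p* of each arm with the highest propensity to seek treatment is excluded; propensity and outcome are bivariate normal with correlation *r* from 0.5 to 0.85; *p* is 5% in one arm and 15% in the other.

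The mean of the retained patients falls by r × SD × λ(p), where λ(p) = φ(z)/(1 − p) and z is the (1 − p) normal quantile.

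- λ(0.15) = 0.2332/0.85 = 0.2743
- λ(0.05) = 0.1031/0.95 = 0.1086
- difference = 0.1657

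Shift in the between-arm difference = r × SD × 0.1657:

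| r | SD 2.5 | SD 3.16 |
|---|---|---|
| 0.3 (weak link) | 0.12 | 0.16 |
| 0.5 | 0.21 | 0.26 |
| 0.7 | 0.29 | 0.37 |
| 0.85 | 0.35 | 0.45 |

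The arm that loses more patients looks better. If both arms lose the same proportion, the λ terms cancel and the shift is 0.

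**3. False-positive rate at r = 0.5.** Retained numbers are 46 × 0.95 = 43.7 and 46 × 0.85 = 39.1. In SD units the shift is 0.5 × 0.1657 = 0.083, and the standard error is √(1/43.7 + 1/39.1) = 0.220, a ratio of 0.376. The two-sided 5% test then rejects with probability of about 0.066. With equal exclusion it stays at 0.05.

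**4. A true difference of 2.5 points (the planning value).** With one common threshold for seeking treatment, the worse arm loses more patients. At 15% excluded overall and r from 0.85 to 0.5, the observed difference is about 1.88 to 2.28 points; at 5% overall, about 2.19 to 2.39. At r = 0.3 the figures are 2.42 and 2.46. In this case the bias is attenuation.

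**5. The alternative of keeping everyone.** Under the settings of step 4 at 15% use, suppose the medication itself lowers RMDQ by 1 or 2 points (assumed). The difference in all randomised patients is 2.5 minus the drug effect times the difference in use between arms. For SD 2.5 and r = 0.85, use is 6.0% and 24.0%, so a 2-point effect gives 2.5 − 2 × 0.18 = 2.14. Over the two SDs, r from 0.85 to 0.5 and both drug effects, the range is about 2.14 to 2.41, which overlaps the range in step 4.

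**The case against.** The strongest reply is that no conflict has been shown. Where the authors meant removal from the analysis they named the analysis, and here they did not. The sentence directly before the rule is the ban on other treatment; the intention-to-treat wording closes the previous paragraph and concerns attendance and home exercise. The sentence after the rule deals with leaving the study and changing the intervention. This stands: exclusion from the analysis is plausible, not established. It does not remove the point, because the rule is printed, acts after randomisation, and can be applied as written to drop patients. It is a stated rule, not a detail left to a fuller document.

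A second reply is that one statement on analysing everyone as randomised would settle both this and the attendance rule. That is fair as to the remedy, and the two should be corrected together. The triggers still differ, so each sentence needs changing.

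Three stronger inferences are not supported:

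- *That the protocol certainly removes these patients from its analysis.* The object of the exclusion is not stated.
- *That the bias is large or favours one arm.* The article gives no rate of other treatment in either arm. Larger shifts would need a larger SD than the article gives, more unequal rates or a closer link to outcome.
- *That the entry wording settles the meaning.* Participants describes patients "who are not currently undergoing any type of treatment", while Inclusion criteria asks only that they are "not receiving any other physiotherapy treatment". That difference concerns eligibility and does not show what a patient is later excluded from.

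**Conclusion.** The point holds as a request for clarification. The article sets a post-randomisation exclusion for medication or other treatment and does not say what the exclusion is from. If it is from the analysis, it conflicts with the declared intention-to-treat principle and can bias the primary comparison; if it only stops study treatment, there is no conflict.

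Under the assumed 5% versus 15% exclusion with no true difference, the shift is about 0.2 to 0.45 RMDQ points, or about 8% to 18% of the 2.5-point planning difference (0.21/2.5 and 0.45/2.5). It is smaller with a weaker link to outcome and zero with equal exclusion. This rests on the article's two SDs, on correlations of 0.5 to 0.85 and on exclusion rates chosen for illustration.

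**What to change.** Replace the exclusion sentence under Interventions with: *Patients who take medication or receive other treatment stay in follow-up and are analysed in their randomised arm.* Record such use at the two planned post-treatment assessments (1 day after the final session and 2 months after the end of the intervention) and report it by arm. Show results without these patients only as a sensitivity analysis. Correct the attendance and home-exercise condition in the same section at the same time.

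The ban on other treatment can stay as a clinical instruction; that is for the investigators to decide.

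The cost is one sentence and one short question at two visits already planned. The drawback is that the main estimate then includes the effect of any medication taken. As step 5 of the working shows, the gain is that the randomised groups stay intact, not a demonstrated gain in numerical accuracy.
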